**Figure 3 figure3:**
[figure not shown]
Identifying differentially expressed genes (DEGs) and pathways activated by the treatment in objective 1 of the study protocol. IGF-1: insulin-like growth factor 1. LC-MS/MS: Liquid chromatography with tandem mass spectrometry; RNA-Seq: RNA sequencing.

The steps for the RNA-Seq include the following:

Total RNA will be extracted using a RNeasy extraction kit, with on-column DNase digestion.RNA quality will be assessed using an Agilent bioanalyzer.Samples will be analyzed on an Illumina HiSeq platform using standard protocols.For quantitative reverse transcriptase PCR validation of RNA-Seq results, a subset of the groups described in objective 1 will be used.The expression of identified differentially expressed genes will be compared in the publicly available RNA sequencing databases.

At the same time, we will use phosphoproteome analysis to identify differentially phosphorylated proteins between different study conditions using liquid chromatography with tandem mass spectrometry measurement.

The steps involved in the phosphoproteomics will be as outlined below:

Cell lysis, protein digestion, and labellingPeptide enrichment, immunoprecipitation, and offline fractionationMass spectrometry data acquisitionPeptide and protein database searchingProteomics data analysisPhosphoproteomics and acetyl-immunoprecipitation data analysis

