### Objective 3: Bioinformatics

We will perform bioinformatics pathway analysis to identify any key genes and proteins involved in the association between PCOS and EC, after transcriptomic and phosphoproteomics profiling, as identified in objective 2 (Figure 4). The results from the same HEC-1-B and HEC-1-A cell lines and treatment groups, as outlined in objectives 1 and 2, will be used.

The methodology for the RNA-Seq data analysis will be as previously published [26], paired end raw reads (FASTQ format) will be quality- and adapter-filtered using Trim Galore wrapper for FastQC and Cutadapt [27]. The retained paired reads will be aligned to the Ensembl-annotated HG19 human Illumina iGenome build using Tophat2. Subsequently, differential gene expression will be calculated for the different cell culture study groups in comparison to the control specimen, using Cuffdiff, based on fold changes >1.5 and a *P* value <.05. Statistically significantly enriched gene ontologies and pathways for differentially expressed genes will be obtained using WebGestalt and the Cytoscape GeneMANIA plug-in. Next-generation RNA-Seq and associated clinical information will be obtained from publicly available data sets.

The methodology for the phosphoproteomics data analysis will also be as previously published data analysis for the phosphoproteomics data; label-free quantitative data will be filtered with a cutoff of ≥2 observations in the 4 repeats of at least 1 time point. Log transformation will be performed before any missing data points are imputed using random values generated from a normal distribution centered at the 1% quantile and the median SD. The abundance of phosphopeptides will be normalized to the abundance of corresponding parental proteins. The Limma package will be used in the R environment to identify differential proteins or phosphorylation with a false discovery rate–corrected ANOVA *P* value of .05. The k-means clustering approach will be used to analyze the patterns of the differential proteins and phosphorylation events. For functional annotation and network analysis, the differentially regulated proteins will be searched against the String database, and the networks will be visualized by using Cytoscape.

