Although the study will aim to recruit 20 women with PCOS and 20 women without PCOS aged between 18 and 45 years, we will begin with a pilot study of samples from 3 women with PCOS and 2 controls and perform validation studies in the larger cohort of 20 women with PCOS and 20 women. The experimental plate design for the cell-culture studies in this feasibility study is illustrated in Table 1.

It will be 1 plate per cell line for each time point (24 h and 48 h). All experiments will be conducted in quadruplicates. We recognize that opinions differ about the ideal sample size for cell-culture experiments [28]; however, we believe our proposed experiments are stringent enough to make the results believable.

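### The phosphoproteomics plan is both labelled and label-free, and its time-point filter with low-value imputation can turn detection gaps into apparent differences between treatment conditions

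*Protocol article*

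**What the plan says.** All references are to the protocol article.

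- **Quantification method.** Under Objective 2, the first phosphoproteomics step combines cell lysis, digestion of the protein and labelling. Under Objective 3, the data to be analysed are described as label-free.
- **Filter.** Objective 3 states that "label-free quantitative data will be filtered with a cutoff of ≥2 observations in the 4 repeats of at least 1 time point".
- **Imputation.** After log transformation, "any missing data points are imputed using random values generated from a normal distribution centered at the 1% quantile and the median SD".
- **Test.** Limma is used to "identify differential proteins or phosphorylation with a false discovery rate–corrected ANOVA" P value of .05. The differential features then go to k-means clustering, and the differentially regulated proteins to a String network search.
- **Comparison of interest.** Objective 2 sets out to "identify differentially phosphorylated proteins between different study conditions using liquid chromatography with tandem mass spectrometry measurement".
- **Design.** The cell-line section lists 12 treatment conditions. Objective 3 gives one plate per cell line at each of 24 h and 48 h, and says "All experiments will be conducted in quadruplicates".

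**The concern.** There are two linked problems.

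First, the labelling contradiction is not cosmetic. Replacing a gap with a low value assumes that the gap means low abundance. That is a common working assumption when each sample is measured separately without a label. When labelled samples are pooled and measured together, gaps tend to affect a whole pool at once and say little about abundance in one sample. The imputation rule therefore cannot be judged until the method is settled.

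Second, the filter does not describe this design. With 12 conditions in quadruplicate, one time point holds 12 × 4 = 48 values per cell line, so four repeats of a time point do not identify a set of samples here. Read in the nearest workable way, as four repeats of a condition at a time point, the rule keeps a feature seen twice in one condition and asks for nothing in any other. Every gap is then filled with a low draw, whatever caused it, and limma treats that draw as data. The article states no missingness assumption and gives no check on the imputation.

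At stake is the list of differential phosphoproteins that feeds the clustering and networks for Objectives 2 and 3.

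**Working it through.** The article gives no sample size or error rate for this step, so there is no figure to reproduce. The check has three parts.

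**1. How much of a kept feature can be imputed.** Inputs from the article: 12 conditions, 2 time points, 4 repeats. On the reading above, 12 × 2 × 4 = 96 values per cell line. A feature seen only twice is kept, so (96 − 2)/96 = 94/96 = 98% of its values can be random draws. This ignores donors. Table 1 has 24 donor-by-treatment cells × 4 = 96 wells per plate, or 192 wells per cell line over two time points, and the article does not say how many samples go to mass spectrometry.

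**2. How often one side is empty.** Take two groups of four and a detection probability *d* (assumed).
- P(at least 2 of 4) = *t* = 1 − (1−*d*)⁴ − 4*d*(1−*d*)³
- P(kept) = 1 − (1−*t*)²
- P(other group empty, given kept) = 2*t*(1−*d*)⁴ / P(kept)

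| *d* | *t* | P(kept) | Other group empty |
|---|---|---|---|
| 0.2 | 0.181 | 0.33 | 45% |
| 0.4 | 0.525 | 0.77 | 18% |
| 0.6 | 0.821 | 0.97 | 4% |

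**3. False hits with no true difference.** The stated pipeline was simulated: filter of at least 2 of 4 in at least one group, imputation as written, limma-type moderated F test, Benjamini-Hochberg at .05. Assumptions not in the article: 2,000 features, between-feature SD 2.0 and replicate SD 0.5 on the log scale, and the detection rates below. Normalization to the parental protein was not simulated. Most rows rest on 60 runs and are imprecise.

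| Scenario | Per-test error | Runs with any FDR hit | Mean false hits per 2,000 |
|---|---|---|---|
| 2 groups, nothing missing | 0.049 | 5% | 0.0 |
| 2 groups, missing through low abundance | 0.046–0.050 | 5–7% | 0.1 |
| 4 groups, missing through low abundance | 0.044–0.047 | 5–13% | 0.0–0.1 |
| 12 groups, missing through low abundance | 0.047–0.049 | 15–22% | 0.2–0.3 |
| 2 groups, missing at random, detection 0.8 / 0.6 / 0.4 | 0.030 / 0.055 / 0.066 | 80% / 97% / 87% | 1.7 / 5.0 / 4.2 |
| 4 or 12 groups, missing at random | 0.044–0.059 | 18–45% | 0.2–1.0 |
| 2 groups, detection 0.9 v 0.7 | 0.065 | 98% | about 8 |
| 2 groups, detection 0.9 v 0.5 | 0.21 | 100% | about 70–80 |

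With 12 groups, half detected at 0.9 and half at 0.5, false hits rise to roughly 400 to 450 per 2,000.

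The detection pattern matters. In a two-group comparison of a mid-abundance feature, 2 v 0 gives a median P of about 0.15 and P<.05 in under 2% of cases. A 3 v 0 pattern gives a median P of about 0.03, and 4 v 0 gives about 0.00001.

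**The case against.** The strongest defence is that low-value imputation is coherent when low abundance causes the gaps, and in that scenario the error stays near nominal. The article also says that the analysis follows a published method, where some detail may lie, and an analysis plan may hold sensitivity analyses. Both points stand in part. But the article itself fixes the filter and imputation, and it contradicts itself on labelling. Those are not omissions.

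A reader might infer that the rule necessarily creates false differences. The documents do not support that, because the outcome depends on a missingness mechanism that they do not state. Nor is a feature seen exactly twice the main danger: its own two imputed repeats inflate the within-group variance, so it seldom reaches significance in a two-group comparison. The lenient filter matters because it also admits 3 v 0 and 4 v 0 patterns.

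A reader might also count raw P<.05 among kept features at very low detection. With 12 groups and detection of 2–5%, that gives 8–30%. It is the wrong criterion, because the plan declares hits on FDR-corrected P values. After that correction at most about 2% of kept features are false hits in the same scenario, and the detection rate is itself an extreme assumption.

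Finally, a stricter filter has a price. Requiring detection in half of all samples would remove a phosphopeptide seen in every IGF-1-stimulated, antagonist-free condition and nowhere else (3 of 12 conditions, 25%), which is close to the mechanism under study. That argues for a sensitivity analysis rather than a blanket replacement filter.

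**Conclusion.** The concern holds in a bounded form. Two defects are visible in the text alone: the labelled and label-free descriptions conflict, and the filter refers to time points although the comparison is between treatment conditions. The consequence is conditional: imputing every gap low can turn detection gaps into apparent regulation. Under the assumed settings, FDR-controlled error is near nominal with abundance-driven gaps and mildly inflated with random gaps. It is badly inflated when detection differs between conditions for technical reasons. The article does not show which of these applies. The 12-group results under abundance-driven missingness rest on too few runs to separate a small inflation from none. The effect is confined to the analyses for Objectives 2 and 3. The primary outcome, cell index, is untouched.

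**What to change.** 1. State one quantification method, the same in the Objective 2 steps and the Objective 3 analysis, and confirm that the imputation suits it.
2. Define both the detection filter and the ANOVA factor by treatment condition within time point.
3. Pre-specify a limma sensitivity analysis on observed values only, for example on features with at least 3 of 4 observations in each compared condition.
4. Flag hits that depend on imputed values, and list phosphopeptides present in one condition and absent in another separately, before k-means and String.

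The cost is a little more analysis work and fewer low-abundance phosphopeptides called robust. In a two-group illustration, the rule in step 3 held per-test error at 0.048–0.050. It kept 67% of features at 80% detection, 23% at 60%, and 29% at 0.9 v 0.5. Gaps there were unrelated to abundance; the observed-only analysis was not tested when low values go missing, which is why it is proposed as a sensitivity analysis. The article reports that data analysis has not started, so the change can still be made in advance.

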The primary outcome measure will be the difference in cell proliferation measured by cell index values during the xCELLigence real-time cell proliferation experiment. Comparison of cell index values from cells treated in different groups will be performed by the Kruskal-Wallis test followed by multiple comparison tests.

### Objective 2: Identifying Differentially Expressed Genes and Pathways Activated by the Treatment of Endometrial Cell Lines of the Different Study Groups Listed in Objective 1

We will perform transcriptomic profiling of endometrial cell lines to identify differentially expressed genes in response to different study conditions outlined previously, using RNA Sequencing (RNA-Seq) to identify the molecular targets and pathways involved in the oncogenic effects (Figure 3).

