**Figure 4 figure4:**
[figure not shown]
Bioinformatics pathway analysis to identify any key genes and proteins involved in the association between polycystic ovary syndrome (PCOS) and endometrial cancer (EC).

**Table 1 table1:** Experimental plate design for cell culture studies.

Plates											
1	2	3	4	5	6	7	8	9	10	11	12
PCOS^a^ 1	PCOS 1 + IGF^b^	PCOS 1 + Inhibitor	PCOS 1 + IGF + Inhibitor	PCOS 2	PCOS 2 + IGF	PCOS 2 + Inhibitor	PCOS 2 + IGF + Inhibitor	PCOS 3	PCOS 3 + IGF	PCOS 3 + Inhibitor	PCOS 3 + IGF + Inhibitor
PCOS 1	PCOS 1 + IGF	PCOS 1 + Inhibitor	PCOS 1 + IGF + Inhibitor	PCOS 2	PCOS 2 + IGF	PCOS 2 + Inhibitor	PCOS 2 + IGF + Inhibitor	PCOS 3	PCOS 3 + IGF	PCOS 3 + Inhibitor	PCOS 3 + IGF + Inhibitor
PCOS 1	PCOS 1 + IGF	PCOS 1 + Inhibitor	PCOS 1 + IGF + Inhibitor	PCOS 2	PCOS 2 + IGF	PCOS 2 + Inhibitor	PCOS 2 + IGF + Inhibitor	PCOS 3	PCOS 3 + IGF	PCOS 3 + Inhibitor	PCOS 3 + IGF + Inhibitor
PCOS 1	PCOS 1 + IGF	PCOS 1 + Inhibitor	PCOS 1 + IGF + Inhibitor	PCOS 2	PCOS 2 + IGF	PCOS 2 + Inhibitor	PCOS 2 + IGF + Inhibitor	PCOS 3	PCOS 3 + IGF	PCOS 3 + Inhibitor	PCOS 3 + IGF + Inhibitor
Control 1	Control 1 + IGF	Control 1 + Inhibitor	Control 1 + IGF + Inhibitor	Control 2	Control 2 + IGF	Control 2 + Inhibitor	Control 2 + IGF + Inhibitor	Media (FBS^c^)	Media (FBS) + IGF	Media (FBS) + Inhibitor	Media (FBS) + IGF + Inhibitor
Control 1	Control 1 + IGF	Control 1 + Inhibitor	Control 1 + IGF + Inhibitor	Control 2	Control 2 + IGF	Control 2 + Inhibitor	Control 2 + IGF + Inhibitor	Media (FBS)	Media (FBS) + IGF	Media (FBS) + Inhibitor	Media (FBS) + IGF + Inhibitor
Control 1	Control 1 + IGF	Control 1 + Inhibitor	Control 1 + IGF + Inhibitor	Control 2	Control 2 + IGF	Control 2 + Inhibitor	Control 2 + IGF + Inhibitor	Media (FBS)	Media (FBS) + IGF	Media (FBS) + Inhibitor	Media (FBS) + IGF + Inhibitor
Control 1	Control 1 + IGF	Control 1 + Inhibitor	Control 1 + IGF + Inhibitor	Control 2	Control 2 + IGF	Control 2 + Inhibitor	Control 2 + IGF + Inhibitor	Media (FBS)	Media (FBS) + IGF	Media (FBS) + Inhibitor	Media (FBS) + IGF + Inhibitor

^a^PCOS: polycystic ovary syndrome.

^b^IGF: insulin-like growth.

^c^FBS: fetal bovine serum.

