## Results

In this study, we have described the protocol for an ongoing study to investigate the role of IGF-1 in mediating the risk of EC in women with PCOS. The study will aim to recruit 20 women with PCOS and 20 controls and measure the effect of serum from these women on cell proliferation and molecular pathways in human EC cell lines, compared with IGF-1 and IGF-1 antagonists. Recruitment for the study is currently ongoing. The project was funded in June 2022 and approved by the Mohammed Bin Rashid University of Medicine and Health Sciences’ IRB in October 2022; funds were released in January 2023, and data collection began on 16 March 2023 and is ongoing. Three women with PCOS and 2 controls have been recruited as the date of this submission from 1 hospital site and IRB permission for further participant recruitment at a second hospital site was granted in October 2023. Data analysis has not yet commenced. We anticipate that initial results for analysis and publication will be available by the summer of 2024.

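### The 20 + 20 comparison must span several culture plates, but the stated primary test has no plate term

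*Protocol article*

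**What the plan says.** Under Objective 3 of the protocol article, "the study will aim to recruit 20 women with PCOS and 20 women without PCOS aged between 18 and 45 years". The same sentence then sets out two stages, a small first one before the main cohort: "we will begin with a pilot study of samples from 3 women with PCOS and 2 controls and perform validation studies in the larger cohort". The layout is given for that pilot: "The experimental plate design for the cell-culture studies in this feasibility study is illustrated in Table 1". There is one plate per cell line at each of 24 h and 48 h, and "All experiments will be conducted in quadruplicates". Table 1 has 8 rows and 12 columns. It holds three PCOS sera, two control sera and a media block, each alone, with IGF, with inhibitor and with both.

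The primary outcome is the difference in cell proliferation measured by cell index. Its analysis is stated at the end of the account of Objective 1: "Comparison of cell index values from cells treated in different groups will be performed by the Kruskal-Wallis test followed by multiple comparison tests". No plate block, stratification or normalisation to the media wells is named there. No layout is given for the 20 + 20 cohort.

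**The concern.** A Kruskal-Wallis test ranks all values together and compares the groups. That suits a single plate. Once the women are spread over several plates, differences between plates in, for example, cell passage, seeding density or reagent lot shift every well on a plate together. A test with no plate term cannot separate these shifts from differences between women.

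Quadruplicate wells do not help, because in Table 1 all four wells of a condition sit on the same plate and share its conditions. With both groups on each plate, the shifts inflate the variance and cost power in the primary comparison. If the groups were unevenly spread over plates, they could also bias it.

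**Working it through.** **Inputs.** From Table 1: 8 × 12 wells; 5 sera; 4 treatments per serum; 4 wells per treatment; one media block with the same 4 treatments. From Objective 3: 20 + 20 women, one plate per cell line and time point in the pilot, two time points. From the cell-line section: two lines.

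**Step 1: reproduce the pilot plate.**
- Wells per serum: 4 × 4 = 16.
- Five sera: 5 × 16 = 80. Media: 4 × 4 = 16.
- Total: 80 + 16 = 96 = 8 × 12. The plate is full.

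**Step 2: plates needed for 40 women, per cell line and time point.**
- Media on every plate: 40 / 5 = 8 plates, or 8 × 2 × 2 = 32 over both lines and both times.
- Media run only once: (40 × 16 + 16) / 96 = 656 / 96 = 6.8, so 7 plates.
- Pilot women additional to the 40: 45 / 5 = 9 plates.

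The count depends on the reading, but every reading needs several plates.

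**Step 3: what the stated test loses.** The article gives no alpha, effect size or variance for cell index, so this step rests on assumptions. One value per woman = group effect + plate effect + woman effect, with normal plate and woman effects and between-woman SD = 1. The plate SD is set at 0, 0.5, 1 and 2. The group effect is 0.89 SD, borrowed only for illustration from the standardised mean difference in serum IGF-1 quoted under Prior Work; it is not an estimate for cell index. Two-sided 5% tests, PCOS against control for one condition, 4,000 runs. Eight plates alternate 3 PCOS + 2 controls with 2 + 3.

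| Plate SD / woman SD | Kruskal-Wallis, no plate: false-positive rate | Kruskal-Wallis, no plate: power | Linear model with plate: power | Rank test stratified by plate: power |
|---|---|---|---|---|
| 0 | 0.05 | 0.77 | 0.77 | 0.68 |
| 0.5 | 0.03 | 0.68 | 0.76 | 0.67 |
| 1 | 0.02 | 0.50 | 0.76 | 0.68 |
| 2 | 0.003 | 0.19 | 0.77 | 0.68 |

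Both plate-blocked tests held a false-positive rate of 0.05 to 0.06. Simulation error on the power figures is about 0.01. With only five women per plate, the stratified rank test gives up some power whatever the plate SD, and overtakes the plain test only when plate variation is larger than about half the between-woman SD.

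**Step 4: when the problem becomes bias.** If each group were run on its own plates (four all-PCOS, four all-control), the plain test's false-positive rate rises to about 0.14, 0.28 and 0.38 at plate SD 0.5, 1 and 2. With both groups on most plates but in moderately uneven numbers, and plate effects that are random rather than drifting, it stays at about 0.03 to 0.05.

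**The case against.** The strongest reply is that Table 1 is expressly the feasibility layout and that the pilot exists to find methodological problems before the main cohort. An article may leave the main layout and any normalisation to the full protocol. That stands: the absence of a main-cohort layout is not itself a fault.

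Three stronger readings do not hold.
- A reader might infer that 3 + 2 will be repeated until PCOS sera run out, leaving controls alone on the last plate. The article does not say that the pattern will be repeated. Nor does it say that plates follow recruitment order; serum is stored at –80˚C, so they need not.
- A reader might infer that raw cell index values are declared to be pooled across plates. The text names a test and is silent on pooling; normalising to media beforehand would be compatible with it.
- A reader might infer an inflated false-positive rate. With both groups on the plates and random plate effects, the simulation shows none.

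What the reply does not remove is that the article does commit to a primary test, that this test is one-way, and that the cohort cannot fit on one plate.

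**Conclusion.** The concern holds in limited form: a stated test is poorly matched to a comparison that must span several plates (8 per line and time point with media on each). The expected cost is lost power. Under the assumptions in the working, it falls from about 0.77 to 0.68, 0.50 or 0.19 as the plate SD goes from 0.5 to 2 times the between-woman SD; if plates hardly differ, the loss is negligible. Balance alone does not prevent it, since these figures already assume balanced plates.

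Bias would require either groups run on separate plates, or groups unevenly spread over plates that drift over time. The article proposes neither and rules out neither. The size rests on an assumed plate SD and a borrowed effect; the direction does not. The point is worth acting on because the Results section reports that analysis has not begun, and plate allocation cannot be repaired afterwards.

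**What to change.** 1. **Layout (Objective 3).** State that every main-cohort plate carries both groups and the media block. For example, for each cell line and time point use four plates of 3 PCOS + 2 controls and four of 2 PCOS + 3 controls. This gives 4 × 3 + 4 × 2 = 20 PCOS and 4 × 2 + 4 × 3 = 20 controls on 8 plates. Say whether the five pilot women count among the 40; if they do, the pilot plate can be one of the four 3 + 2 plates.
2. **Primary analysis (end of Objective 1).** For PCOS against control, replace the plain Kruskal-Wallis test with a plate-blocked comparison of one value per woman (the mean of her four wells). Use a linear mixed model with plate or, if a rank method is preferred, a rank test stratified by plate. With five women per plate the linear model is the more powerful where its assumptions are reasonable.
3. **Media normalisation is optional.** Dividing all values on a plate by that plate's media mean leaves within-plate ranks unchanged, so it adds nothing to a stratified rank test.

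The cost is a short paragraph and a sentence, with no additional plates, sera or women. The small downside is that sera stay frozen until a mixed set of five is available.
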